#### Independently upgraded controls

We anticipate some of the control compounds may have independently upgraded their sanitation facilities to conditions comparable to the intervention. Control compounds with sanitation facilities observed to possess cleanable, intact hardscape slabs; pour-flush or water-sealed toilets; a functional ventilation pipe; and a fixed superstructure with sturdy walls and a secure door that ensure privacy during use are considered to have independently upgraded to conditions comparable to the intervention.^55^ Children living in control compounds with independently upgraded latrines are enrolled but will be excluded from the main analyses of the intervention effects. Two sets of subgroup analyses will instead be conducted that include all participants: one in which children in independently upgraded controls are considered as part of the control (non-intervention) arm and again considered as part of the intervention arm. We will compare parameter estimates from the three sets of analyses to investigate whether the sanitation improvements independently available in the study communities are comparable to the full sanitation intervention package assessed in the MapSan trial in terms of child health impacts.

Eligible children residing in any compound that has received a WSUP intervention latrine will be considered part of the intervention arm in primary analyses. We record the current conditions of intervention facilities but will not exclude or otherwise adjust for either upgraded or degraded sanitation facilities in intervention compounds in order to evaluate the long-term impacts of the intervention following extended use.

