## Abstract

**Introduction:**

We previously assessed the effect of an onsite sanitation intervention in informal neighbourhoods of urban Maputo, Mozambique on enteric pathogen detection in children after 2 years of follow-up (Maputo Sanitation (MapSan) trial, ClinicalTrials.gov: NCT02362932). We found significant reductions in *Shigella* and *Trichuris* prevalence but only among children born after the intervention was delivered. In this study, we assess the health impacts of the sanitation intervention after 5 years among children born into study households postintervention.

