**Trial registration number:**

ISRCTN86084138.

STRENGTHS AND LIMITATIONS OF THIS STUDYLong-term follow-up of an urban on-site sanitation intervention implemented at least 5 years prior so that all participants have been exposed to the treatment conditions for their entire lives.Primary study endpoint is molecular detection of multiple enteric pathogens in child stool, which unambiguously indicates previous exposure to specific sanitation-related pathogens.Primary outcome is the overall impact of the intervention on enteric pathogen exposure using a novel pooled estimate of the treatment effect across a prespecified set of enteric pathogens.As an observational evaluation of an existing intervention, sample size is constrained by the number of eligible children residing at study sites and selection bias arising from differential enteric pathogen-related mortality may be present, particularly among older age groups.As a cross-sectional study, there is potential for confounding bias in our estimates of the intervention impacts on child health, particularly as the intervention itself may have influenced the desirability of the intervention sites and thus the socioeconomic status of their residents, which may be associated with reduced pathogen exposures.

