### Eligibility criteria

We attempt to enrol all eligible children in each compound that either previously participated in the MapSan trial, has previously received an intervention latrine, or meets the original enrolment criteria for MapSan control compounds.^34^ Participant inclusion criteria include:

Child aged 29 days to 60 months old.Born into and residing in a compound enrolled in the 5-year follow-up study; in intervention compounds, the child must have been born following the delivery of the sanitation intervention.Has continuously resided in the study compound for the preceding 6 months, or since birth if under 6 months of age.Has a parent or guardian who is able to understand and complete the written informed consent process and allow their child to participate.

Children are excluded if they have any caregiver-indicated medical condition or disability that precludes participation in the study.

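### The analysis that counts upgraded controls as intervention has no birth-after-upgrade rule, so it can include partly exposed children and make upgrades look less comparable than they are

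*Protocol article*

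**What the plan says.** The protocol article uses two different timing rules for exposure.

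- **WSUP compounds.** Under Eligibility criteria, "in intervention compounds, the child must have been born following the delivery of the sanitation intervention". The follow-up also requires the facility to be at least 5 years old (Long-term cross-sectional follow-up study), and the age criterion is "Child aged 29 days to 60 months old". The list of strengths presents the result as an advantage: the follow-up is long "so that all participants have been exposed to the treatment conditions for their entire lives".
- **Upgraded control compounds.** Under Independently upgraded controls, the class is defined by what is seen: "Control compounds with sanitation facilities observed to possess cleanable, intact hardscape slabs", together with toilet type, ventilation and superstructure. No upgrade date or minimum time since upgrade is set. Children in these compounds are left out of the main analyses. "Two sets of subgroup analyses will instead be conducted that include all participants", in which "children in independently upgraded controls are considered as part of the control (non-intervention) arm and again considered as part of the intervention arm".

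The other timing condition on a control-compound child, besides being born into the compound, is residence: "Has continuously resided in the study compound for the preceding 6 months, or since birth if under 6 months of age". That concerns the compound, not the age of its toilet.

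The three sets of estimates are then compared to judge whether locally available upgrades match the intervention package in their effect on child health.

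**The concern.** The restriction to children born into the facility has a reason. The abstract reports that the earlier trial found reductions in *Shigella* and *Trichuris*, "but only among children born after the intervention was delivered". If timing of exposure matters for WSUP facilities, it should matter for independent upgrades too.

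As written, a 50-month-old whose compound upgraded two months before the survey enters the as-intervention analysis on the same footing as a child who has lived with a WSUP toilet since birth. Facility type is then mixed with timing of exposure. If exposure from birth works better than exposure begun later, an upgrade that is just as effective will tend to look inferior.

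What is at stake is the comparability conclusion, which has a direct policy reading: whether upgrades that residents make themselves do as well as the programme's facilities.

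**Working it through.** The plan states no figure on this point, so there is none to reproduce. The check compares the rules and then illustrates the size.

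**Step 1. The rules side by side.**

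| | WSUP compound | Upgraded control, counted as intervention |
|---|---|---|
| How exposure is assigned | Receipt of a WSUP facility at least 5 years earlier | Facility features observed |
| Birth after the improvement | Required | Not required |
| Residence | 6 months, or since birth | Same |
| Children included | Those meeting the birth rule | All |

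**Step 2. Share born before the upgrade (f).** Input from the article: ages 29 days (0.95 months) to 60 months. Assumptions: ages uniform; upgrade times uniform over the last U months and independent of age.

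f = P(age > time since upgrade) = E[min(age, U)] / U

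- U = 72: E[age] = (0.95 + 60)/2 = 30.5, so f = 30.5/72 = 0.42.
- U = 36: E[min(age, 36)] = [(36² − 0.95²)/2 + 36 × 24]/59.05 = (647.5 + 864)/59.05 = 25.6, so f = 25.6/36 = 0.71.

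The window U is an assumption. A simulation with ages 1 to 60 months gave f of 0.81 for U = 24, 0.51 for U = 60 and 0.36 for U = 84.

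**Step 3. Effect on the merged intervention arm.** Assumptions: one pathogen; true PR of 0.75 in children born into either type of facility; children born before the upgrade treated as fully unexposed (PR 1.0, the worst case); equal background prevalence; 400 WSUP children (the article's minimum per arm); and 400 × s upgraded-control children added, with s from 0.1 to 0.3.

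PR among upgraded-control children: g = f × 1 + (1 − f) × 0.75

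Merged-arm PR = (400 × 0.75 + 400 × s × g) / (400 + 400 × s)

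| f | g | s = 0.1 | s = 0.3 |
|---|---|---|---|
| 0.42 | 0.855 | 334.2/440 = 0.76 | 402.6/520 = 0.77 |
| 0.71 | 0.928 | 337.1/440 = 0.77 | 411.3/520 = 0.79 |

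For a true PR of 0.50 and f from 0.25 to 0.75, the same formula gives 0.51 to 0.59.

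**Step 4. With a birth-after-upgrade rule.** f becomes 0, g equals the true PR, and the merged arm stays at 0.75. This source of bias disappears.

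**The case against.** Much can fairly be said for the plan.

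- **The primary estimate is untouched.** A reader might infer that the main intervention effect is biased, or that the main analysis wastes valid controls. The article does not support either reading. Upgraded-control children are excluded from the main analyses, which is a defensible way to handle contaminated controls, and an analysis that keeps all of them as controls is already planned.
- **The children are partly exposed, not unexposed.** They live with the upgraded facility now. The evidence that birth timing matters is an exploratory subgroup result, as the article says. Setting their PR to 1.0 is therefore a worst case.
- **No estimate is planned for upgraded-control children alone.** A reader might take the g values in the working (about 0.86 to 0.93) as what the study would report. The plan compares whole-arm estimates, where the shift is 0.01 to 0.04.
- **The two allocations can be read as bounds.** The Limitations section calls them sensitivity analyses for exposure misclassification. That reading stands, but the statistical section also uses them to judge comparability, and for that purpose the asymmetry matters.
- **Age is adjusted for and examined by stratum.** Under the same assumptions, only about 9% (6.5/72) to 18% (6.5/36) of children aged 1–11 months would predate the upgrade. Strata could help, but the article does not tie them to these analyses, and adjusting for age does not equalise exposure at a given age.
- **The affected group may be small.** Newly recruited controls must meet the original criteria, including shared sanitation in poor condition, so upgraded controls should come mainly from former trial compounds.
- **Upgrade dates may already be collected.** The compound questionnaire and the data analysis plan are not shown, and the article says upgrades are monitored. Even so, analyses that take in all participants leave no restriction by birth date.

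**Conclusion.** The concern holds for the secondary as-intervention analysis and the comparability conclusion drawn from it, and no further. Followed exactly, the stated rule applies a birth-timing condition to WSUP children and none to upgraded-control children. The direction of bias is towards upgrades looking less comparable to the full intervention, provided that exposure from birth protects more than exposure begun later. If timing made no difference, there would be no bias.

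The size cannot be determined from the article. In the illustration, 42% to 71% of upgraded-control children predate the upgrade, and a merged-arm PR of 0.75 moves to at most about 0.76 to 0.79. That is small next to the 25% reduction that the article gives as detectable at 34%–46% baseline prevalence. It nonetheless falls on the contrast between the three sets of estimates, which is the article's stated way of judging comparability, and nothing in the described analysis would reveal it. These figures rest on uniform ages, evenly spread upgrades, 10% to 30% of 400 children in upgraded controls, and no benefit at all for children born before the upgrade.

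**What to change.** 1. Where a control compound meets the upgrade criteria, obtain the approximate month and year of the upgrade in the compound questionnaire, if this is not already recorded.
2. In the analysis that counts upgraded controls as intervention, include only children born after the upgrade, so that the same birth rule applies to both types of facility.
3. Report children born before the upgrade separately, with their number.
4. If dates cannot be obtained, state beside the comparability conclusion that upgraded-control children may have been exposed for only part of their lives and that this favours finding upgrades less comparable.

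The main analysis needs no change. The cost is one compound-level question and a sentence in the analysis plan. The drawbacks are recall error in the upgrade date and a smaller upgraded group, hence a less precise comparison.

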#### Minimum detectable effect size

The number of participants will be constrained by the number of compounds in the study neighbourhoods that have received the sanitation intervention or meet the eligibility requirements for MapSan control compounds, most of which were previously enrolled in the MapSan trial. At the 24-month follow-up, an average of 2.5 children per compound were enrolled from 408 compounds.^34^ Compound-level intraclass correlation coefficients were generally less than 0.1 for individual pathogens, corresponding to cluster variances of ~0.05. We calculate the minimum detectable effect size (MDES) on individual pathogen prevalence with 80% power, 5% significance level and 0.05 compound cluster variance for a conservative scenario with 200 compounds per treatment arm and 2 children enrolled per compound (for 800 children total, 400 per arm), a moderate scenario of 220 compounds per treatment arm and 2.5 children enrolled per compound (550 children per arm, 1100 total), and a maximal scenario of 300 compounds per arm, 2.5 children per compound (750 children per arm, 1500 total).^108^ Across all scenarios, a minimum baseline (untreated) prevalence of 6–8% is required to reach 80% power for even the largest theoretical effect (nearly 100% reduction). The minimum detectable relative reduction in prevalence decreases (ie, smaller effect sizes are more readily detected) as pathogen prevalence increases towards 100% (figure 1). The difference between the scenarios on the multiplicative scale is relatively minor, with the relative reduction MDES largely driven by pathogen baseline prevalence. A pathogen with baseline prevalence below 15% must have its prevalence halved (PR<0.5) in order to attain 80% power, while a 25% reduction is detectable with 80% power for baseline prevalence of 34%–46% under the maximal and conservative scenarios, respectively. We expect the simultaneous consideration of multiple pathogens to reduce the MDES for the primary outcome pooled intervention effect by effectively increasing the sample size. Because this pooled effect is dependent on the prevalence of each pathogen considered and the correlations between them, we will conduct simulation analyses to characterise plausible MDES ranges for the pooled primary outcome treatment effect.^68 108^

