Because childhood diarrhoea is a leading cause of child mortality, selection bias arising from survivor effects may be present in our sample, particularly among older age groups.^109^ However, loss to follow-up due to mortality was exceptionally rare in the previous assessment—far less common than emigration, which was not previously differential by treatment arm.^34^ Our use of stool-based enteric pathogen detection as an objective primary outcome mitigates the potential for measurement bias^36^ and we are assessing multiple negative control outcomes to account for potential response bias in our secondary caregiver-reported outcomes.^78^ As a long-term evaluation of an existing intervention, the potential for exposure measurement error is low—interventions that have degraded substantially may shift results towards the null, but in so doing would represent a valid assessment of intervention sustainability.^110^ The potential for exposure misclassification among controls is higher, in that they may have independently upgraded to sanitation infrastructure comparable to the intervention. We are actively monitoring this possibility at all study sites; have prespecified criteria for identifying sites achieving such conditions; and will conduct sensitivity analyses with these sites excluded, considered as controls, and considered as equivalent to the intervention to characterise the impact of any such potential exposure misclassification among controls.

A key challenge is identifying an appropriate set of outcomes against which to evaluate the intervention; in this regard, we preferred inclusivity given the pathogens likely to be observed in our study setting, at the risk of unduly shifting our eventual results towards the null. This challenge persists, regardless of study design, so long as the study aims include assessing the effect of some condition or intervention on exposure to, or infection by, multiple pathogens that share a common route of transmission.^111^

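### Comparability of independent upgrades is to be judged from three re-labelled intervention-vs-control estimates, none of which is the upgraded-vs-intervention contrast or gives an interval for it

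*Protocol article*

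**What the plan says.** The protocol article treats this under Statistical analysis, Independently upgraded controls. It expects such compounds to exist: "We anticipate some of the control compounds may have independently upgraded their sanitation facilities to conditions comparable to the intervention". It does not say how many. For the main analysis, "Children living in control compounds with independently upgraded latrines are enrolled but will be excluded from the main analyses of the intervention effects". Everyone is then included in two further sets of analyses: "one in which children in independently upgraded controls are considered as part of the control (non-intervention) arm and again considered". The second of these sets counts them with the intervention compounds. The stated purpose is comparability: "We will compare parameter estimates from the three sets of analyses to investigate whether the sanitation improvements independently available". The yardstick named there is the programme's full package, judged on child health.

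The Limitations section gives the same three analyses another job. There the investigators "will conduct sensitivity analyses with these sites excluded, considered as controls, and considered as equivalent to the intervention to characterise the impact". The impact meant is that of exposure misclassification among controls.

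For the comparability question, the article states no direct contrast of upgraded with intervention or with non-upgraded compounds, no margin, and no rule for reading the three estimates together.

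**The concern.** The comparability question concerns one contrast: upgraded control compounds (U) against intervention compounds (I). The three planned estimates all contrast intervention with control (C) and differ only in where the upgraded children sit. How far an estimate moves when they are re-labelled depends both on how well upgrades work and on how many children are re-labelled. If few compounds upgraded, the three estimates will be close whatever the upgrades achieve.

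The interval printed beside each estimate does not help, because it describes intervention versus control. The three estimates also share most of their data, so overlap of their intervals is the wrong yardstick for the differences between them.

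At stake is a policy-relevant statement on whether upgrades available in the community match the programme. Three similar ratios could be taken as support when the data are in fact inconclusive.

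**Working it through.** **Inputs.** The article's Minimum detectable effect size section supplies the planning values: "with 80% power, 5% significance level and 0.05 compound cluster variance for a conservative scenario with 200 compounds per treatment arm and 2 children" per compound. It also puts compound-level intraclass correlations generally below 0.1 and takes a 25% reduction as its worked effect. The upgraded share *f* is not given, so 5% to 50% is assumed. The illustration assumes 400 children per arm, C = 40% and I = 30% (PR 0.75), one pathogen, no covariate adjustment, and a design effect of 1 + (2 − 1) × 0.1 = 1.1.

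**The plan's own figure first.** The article says a 25% reduction has 80% power at a baseline of 34% (maximal) to 46% (conservative). Use a two-sided z-test on compound means, with variance [2 × 0.05 + (p₁q₁ + p₂q₂)/m]/J.
- Conservative, 46% vs 34.5%: [0.10 + (0.2484 + 0.2260)/2]/200 = 0.00169, SE 0.0411. The ratio is 0.115/0.0411 = 2.80, which is 1.96 + 0.84.
- Maximal: 80% power is reached at about 33%, against the stated 34%.

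The planning figures reproduce.

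**What the three analyses estimate** (unadjusted difference scale). Let *w* be the upgraded share of the enlarged control arm and *v* its share of the enlarged intervention arm. With equal arms, w = f and v = f/(1 + f).
- Dropped: I − C.
- Counted as control: (I − C) + w(C − U).
- Counted as intervention: (I − C) + v(U − I).

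The contrast of interest, U − I, therefore appears only multiplied by *v*. At f = 10%, v = 40/440 = 0.091.

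**Expected PRs (dropped / as control / as intervention).**

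| Upgraded share | Upgrades do nothing (U = C) | Upgrades work fully (U = I) |
|---|---|---|
| 10% | 0.75 / 0.75 / 0.77 | 0.75 / 0.77 / 0.75 |
| 30% | 0.75 / 0.75 / 0.81 | 0.75 / 0.81 / 0.75 |
| 50% | 0.75 / 0.75 / 0.83 | 0.75 / 0.86 / 0.75 |

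At 10% with U = C, the enlarged intervention arm is (120 + 16)/440 = 30.9%, and 0.309/0.40 = 0.773. With U = I, the enlarged control arm is (144 + 12)/400 = 39%, and 0.30/0.39 = 0.769. The largest gaps are about 0.02, 0.06 and 0.11.

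**Same shift, different truths.** The shift to 0.773 means no effect at 10% upgraded. At 30% upgraded it arises with U near 33.9%: (120 + 120 × 0.339)/520 = 0.309. There the upgrades would deliver about three-fifths of the effect, (40 − 33.9)/10. The shift cannot be read without dividing by the share.

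**Which yardstick.** At 10% upgraded, SE(log PR) of the main contrast is √[1.1 × (0.7/120 + 0.6/144)] = 0.105, giving 0.61 to 0.92. The paired shift is much less variable. By the delta method with U = C, its SD on the log scale is about 0.026, and 0.0299/0.0257 gives z ≈ 1.16. The direct contrast has |log 0.75|/0.218 = 1.32 (about 1.19 in simulation). At 30% the figures are 1.83 against 2.03 (1.97 in simulation).

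**Interval overlap in simulation.** With beta-binomial data (intraclass correlation 0.1, 3,000 runs per setting), all three intervals overlapped in every run, whether U equalled I or C. At 10% upgraded, the ordering of the shifts pointed the wrong way in about 23–27% of runs.

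**What the direct contrast would show.** If U = I at 10% upgraded, the illustration gives PR 1.00 with SE √[1.1 × (0.7/120 + 0.7/12)] = 0.266, so 0.59 to 1.68. On the article's conservative planning values it is 0.63 to 1.60, and 0.74 to 1.34 at 30% upgraded. If U = C, power to separate U from I is about 0.29–0.33 at 10% and 0.59–0.64 at 30% (conservative to maximal).

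**The case against.** A reader might infer that the planned comparison cannot show anything, or that it would return a finding of comparability almost whatever the truth. The documents do not support that.
- The article promises only to compare estimates in order to investigate. It states no overlap rule and no default conclusion, and for the pathogen outcomes it says magnitude and uncertainty will be weighed holistically.
- The two opposite truths give opposite patterns. The ordering is right in roughly three-quarters of simulated runs at 10% upgraded.
- Setting a 0.02 gap against the main interval of 0.61 to 0.92 overstates the weakness. Against its own paired variability, the shift has nearly the signal-to-noise of the direct contrast.

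Other points on that side are also fair. The upgraded share is unknown and need not be small. Pooling over 22 pathogens should sharpen the single-pathogen figures, by an amount the article does not allow one to compute. The direct contrast is limited by the same number of upgraded compounds, so it creates no new information. Comparability of upgrades is not among the hypotheses or the primary or secondary objectives.

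All of this stands, and it makes the point smaller. It does not supply what is missing: the article plans no rescaling of the shifts, no joint interval for them, and no estimate on the upgraded-vs-intervention scale. Pooling does not turn any of the three contrasts into that one.

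**Conclusion.** The point holds as a mismatch between question and estimate. The three planned estimates contain upgraded versus intervention only in diluted form, and none of their intervals describes it. Similar estimates are compatible both with true comparability and with a small upgraded group. Under the assumed 40% vs 30% prevalence, the largest gap between estimates is about 0.02 at 10% upgraded, 0.06 at 30% and 0.11 at 50%. The direct PR of intervention to upgraded would be 0.75 or 1.00 in the two extreme cases.

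These sizes rest on an assumed upgraded share, one pathogen, no adjustment and a design effect of 1.1. It is not established that the investigators would read similar estimates as proof of comparability, nor that the shifts are uninformative. The question is ancillary. The primary analysis, which drops upgraded controls, is untouched, and the three analyses remain sound for the misclassification purpose in the Limitations section. This is a worthwhile, nearly free improvement.

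**What to change.** For this question only, fit the same adjusted models with a three-level exposure: intervention, independently upgraded control, non-upgraded control. Report intervention versus upgraded and upgraded versus non-upgraded, each with a 95% interval. Base any statement on comparability on the intervention-vs-upgraded interval, ideally against a margin set before the data are examined, and state in advance that a wide interval will be called inconclusive. Report the number of upgraded compounds and children beside it.

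Keep the three re-labelled analyses, described as the exposure-misclassification sensitivity analyses of the Limitations section, and leave the primary analysis as it is.

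The cost is one extra model per outcome on data already planned for collection, since upgraded children are enrolled and identified by prespecified criteria. The drawback is that the direct interval may be wide (roughly 0.6 to 1.6 for one pathogen at 10% upgraded if upgrades equal the intervention). That width is itself the information a reader needs.
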